### **6.5. Assessment of Blinding**

To evaluate whether the blinding of the assessment was successful, the Bang's method and James's method

were applied. After the post-assessment, independent evaluators were asked, "Which treatment do you think the participant received?" The response options provided were "Guided ICBT," "UC," or "Don't know."

Bang's blinding index ranges from -1 to 1, where 0 indicates perfect blinding. A value of 1 indicates complete unblinding, while -1 suggests that all participants' treatment allocations were incorrectly guessed. If the one-sided confidence interval excludes 0, the study is considered to have insufficient blinding.

Additionally, the James blinding index was calculated to provide further insight into the success of blinding.

The James index is a continuous measure ranging from 0 to 1, where a score of 0.5 indicates perfect blinding.

Higher values suggest a greater deviation from perfect blinding. Confidence intervals for the James index were also calculated to assess the adequacy of blinding.

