## **6.6. Sample Size Calculation**

The target sample size for this study is set at 60 participants, with 30 participants in each group. The rationale for this sample size was determined using the statistical analysis software G\*Power 3.1, based on a calculation for an independent t-test. The effect size (Cohen's  $d = 0.9$ ) was derived from a previous study on ICBT for bulimia nervosa, which reported significant reductions in the frequency of binge eating and purging behaviors compared to the waitlist group. Assuming an expected effect size of 0.9 for this study, with a significance level of 0.05 (two-tailed) and a power of 80% ( $1-\beta$ ), a minimum of 21 participants per group is required.

To account for a dropout rate of 30%, an additional 9 participants per group are anticipated, bringing the required sample size to 30 participants per group. Therefore, the total target sample size for the study is 60 participants. This ensures sufficient power to detect significant differences between the intervention and control groups.

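### Section 6.5 gives the James blinding index the wrong direction: many 'Don't know' answers would be reported as poor blinding, and values below 0.5, which signal unblinding, get no reading

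*Protocol*

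**What the plan says.** Protocol section 6.5 (Assessment of Blinding) names two indices: "To evaluate whether the blinding of the assessment was successful, the Bang's method and James's method" are the tools. After the post-assessment the independent evaluators guess each participant's treatment, with three possible answers: guided ICBT, usual care, or 'Don't know'.

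For Bang's index the section gives a scale, "Bang's blinding index ranges from -1 to 1, where 0 indicates perfect blinding", with 1 as complete unblinding and -1 as all guesses wrong. It also gives a decision rule: "If the one-sided confidence interval excludes 0, the study is considered to have insufficient blinding".

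The James index is added as further information. Its scale is stated as "The James index is a continuous measure ranging from 0 to 1, where a score of 0.5 indicates perfect blinding", followed by "Higher values suggest a greater deviation from perfect blinding". The section then says "Confidence intervals for the James index were also calculated to assess the adequacy of blinding", without a cut-off or a side. No other part of the protocol describes the James index.

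**The concern.** The two sentences on James do not fit each other. If 0.5 is the ideal and the scale runs from 0 to 1, departures can occur in both directions, yet the text describes only the upward one. The upward one is also wrongly labelled: under the method's definition, high values come from 'Don't know' answers or wrong guesses, and low values come from correct guesses.

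This matters because section 3 describes the trial as assessor-blinded and section 5.5 relies on the blinded evaluation team to protect the outcomes. Under section 5.6.3 that team collects the primary outcome by telephone, from participants who know whether they received the program or are waiting for it. Accidental disclosure is plausible, so the blinding check has a real job. A misread James result could make blinding look poor when it held, and would carry no stated warning when it failed.

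**Working it through.** **Inputs.** The three answer categories, the James scale and its stated direction, and the Bang scale come from section 6.5. The illustration uses the planned size from section 6.6: "The target sample size for this study is set at 60 participants, with 30 participants in each group". The protocol cites the James method without printing its formula, so the method's standard definition is assumed.

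**Formulas.**
- James = [1 + P_DK + (1 - P_DK) × K] / 2, where P_DK is the share of 'Don't know' answers.
- K = (P_Do - P_De) / P_De, where P_Do is the observed and P_De the chance-expected weighted disagreement among the remaining answers.
- Weights: correct 0, wrong 0.5. A weight of 0.75 for wrong guesses gave the same results.
- Bang, per arm = (correct - wrong) / n.

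**The protocol's own anchor first.** Random guessing with no 'Don't know' answers: P_Do = 0.5 × 0.5 = 0.25. P_De has two wrong cells, each 0.5 × 0.5 × 0.5, so 0.25. Then K = 0 and James = (1 + 0 + 0)/2 = 0.50. The 0.5 anchor reproduces, as the value for random guessing.

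**The direction.** With balanced arms P_De stays at 0.25 in every row where some guesses are made.
- 80% correct: P_Do = 0.5 × 0.20 = 0.10, K = (0.10 - 0.25)/0.25 = -0.6, James = (1 - 0.6)/2 = 0.20.
- Half 'Don't know', rest random: P_DK = 0.5, K = 0, James = 1.5/2 = 0.75.
- All 'Don't know': P_DK = 1, the K term drops out, James = 2/2 = 1.00.

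| Per arm: correct / wrong / Don't know | P_DK | K | James | Bang, each arm | Section 6.5's reading of James |
|---|---|---|---|---|---|
| 30 / 0 / 0 | 0 | -1 | 0.00 | 1.0 | none given |
| 24 / 6 / 0 | 0 | -0.6 | 0.20 | 0.6 | none given |
| 18 / 12 / 0 | 0 | -0.2 | 0.40 | 0.2 | none given |
| 15 / 15 / 0 | 0 | 0 | 0.50 | 0 | perfect |
| 15 / 0 / 15 | 0.5 | -1 | 0.50 | 0.5 | perfect |
| 8 / 7 / 15 | 0.5 | -0.067 | 0.733 | 0.03 | deviation |
| 7.5 / 7.5 / 15 (expected split) | 0.5 | 0 | 0.75 | 0 | deviation |
| 0 / 0 / 30 | 1 | not needed | 1.00 | 0 | greatest deviation |
| 0 / 30 / 0 | 0 | 1 | 1.00 | -1 | greatest deviation |

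Among rows with no 'Don't know' answers, James falls steadily as correct guessing rises. At a fixed guessing pattern it rises with the share of 'Don't know'. Neither matches the stated direction.

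**Sampling error.** In 5,000 simulated tables at 30 per arm, the central 95% of James values ran from about 0.63 to 0.85 for half 'Don't know' and the rest random, wholly above 0.5. For 80% correct it ran from about 0.10 to 0.30, wholly below 0.5. Both situations would therefore show clearly at this sample size, and the section's wording misreads the first and is silent on the second.

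**Does Bang catch the second?** At 24 correct and 6 wrong of 30, the variance is (0.8 + 0.2 - 0.6²)/30 = 0.0213 and the standard error 0.146. Taking the one-sided interval as 95% (the protocol gives no level), the lower limit is 0.6 - 1.645 × 0.146 = 0.36. It excludes 0, so Bang's rule flags it.

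**The case against.** The strongest reply is that little depends on this sentence. James is introduced as a supplement. Bang's index, in the same section, is oriented correctly and carries the only decision rule, and a largely unblinded team would fail it. The James value comes from the guess table and is not altered by a wrong verbal gloss. All of this stands, and it limits the consequence to how one supplementary statistic is interpreted.

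A reader might go further and infer that a fully unblinded team would pass the James check, or that the protocol ranks the whole scale in reverse. The text does not support either. It states no pass rule or cut-off for James. With 0.5 named as perfect, a value of 0.00 is visibly far from the ideal. Values below 0.5 are left without a reading; they are not declared acceptable.

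It can also be said that the formula is not printed in the protocol. But the method is named and cited, and the check uses only its definition. Even without the formula, an ideal in the middle of the scale cannot be squared with deviation in one direction only.

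Finally, calling 1 complete blinding would be wrong too, because all-wrong guessing also gives 1.00. The correction has to allow for that.

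**Conclusion.** The stated direction of the James index is wrong, and nothing else in the protocol corrects it. Two consequences follow. Data dominated by 'Don't know' answers (James about 0.75 to 1.00, Bang 0) would be reported as poor blinding. Data showing unblinding (James 0.20 at 80% correct, 0.00 at all correct) fall in a range to which the section attaches no meaning. The two indices could then give conflicting messages on the same guesses.

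This is an error in what the protocol chose to fix, not a detail left to an analysis plan. It does not touch the primary mixed model, its ANCOVA sensitivity analysis or the sample size. The conclusion rests on the standard definition of the James index; the sizes rest on 30 per arm with equal guessing behavior in both arms.

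**What to change.** Replace the two sentences on the James scale in section 6.5 with text to this effect:

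> The James index runs from 0 to 1: 0 is complete unblinding, 0.5 corresponds to random guessing, and values towards 1 reflect mostly 'Don't know' (or systematically wrong) answers. Lower values mean worse blinding, and an upper confidence limit below 0.5 indicates insufficient blinding.

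The cut-off is an addition, since the protocol gives none for James. If the statistical analysis plan already sets one, the two should be aligned.

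Report James beside Bang's index by arm. Bang separates 'Don't know' from systematic wrong guessing (0 against -1, both with James 1.00). It also shows a case that James alone misses: half 'Don't know' with every other guess correct gives James 0.50 but Bang 0.5 in each arm.

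Section 6.5 is written in the past tense, so any James interpretation already made should be checked against the corrected scale. The cost is two sentences and, at most, a reread of one reported result. No new data are needed.

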## **6.6. Sample Size Calculation**

The target sample size for this study is set at 60 participants, with 30 participants in each group. The rationale for this sample size was determined using the statistical analysis software G\*Power 3.1, based on a calculation for an independent t-test. The effect size (Cohen's  $d = 0.9$ ) was derived from a previous study on ICBT for bulimia nervosa, which reported significant reductions in the frequency of binge eating and purging behaviors compared to the waitlist group. Assuming an expected effect size of 0.9 for this study, with a significance level of 0.05 (two-tailed) and a power of 80% ( $1-\beta$ ), a minimum of 21 participants per group is required.

To account for a dropout rate of 30%, an additional 9 participants per group are anticipated, bringing the required sample size to 30 participants per group. Therefore, the total target sample size for the study is 60 participants. This ensures sufficient power to detect significant differences between the intervention and control groups.

## **7. Discussion and Conclusion**

In this study, we will conduct the first randomized controlled trial (RCT) to evaluate the effectiveness of therapist-guided internet-based cognitive behavioral therapy (ICBT) for Japanese female patients with bulimia nervosa (BN). While a recent study conducted in the Netherlands included participants with a wide BMI range (19.5–40.0 kg/m^2) and mixed diagnoses, this study adopts focused eligibility criteria, specifically targeting patients with bulimia as the diagnosis and excluding other eating disorders. This approach ensures a more homogeneous study population, thereby enhancing the reliability of treatment effect estimates. A systematic review and meta-analysis of e-therapy for eating disorders highlighted promising improvements in symptoms such as binge eating, vomiting, and laxative misuse but found inconclusive evidence regarding its impact on overeating frequency in BN patients due to heterogeneity in study quality. Recent single-arm studies of ICBT have reported positive outcomes, yet RCTs remain the gold standard for clinical trials, providing the highest level of evidence. Previous studies that included BN patients have not provided effect estimates exclusively for BN, often grouping them with other eating disorders. This RCT addresses this gap by offering insights into the effectiveness of guided ICBT in reducing binge eating and purging frequency and addressing secondary

symptoms in BN patients.

Additionally, this study is the first to explore the effects of ICBT on eating behavior changes in Japan, accounting for the country's unique food culture and healthcare system. By adopting a multicenter design, the study aims to minimize bias and improve the generalizability of its findings, providing culturally relevant evidence that could guide future interventions.

This RCT seeks to validate a Japanese culture–adapted ICBT program for BN and contribute to the limited evidence base regarding its efficacy. Given the low implementation rate of CBT in Japanese psychiatric clinics (6.2%) (Takahashi et al.,2018), this research could pave the way for broader access to early treatment for BN patients. Positive results from this trial could lead to improvements in managing eating disorders, which often become chronic and challenging to treat.

## **8. Declarations**

### **8.1. Publication Rules**

All researchers involved in this study comply with the "Declaration of Helsinki (2013 Fortaleza Revision)" and the "Ethical Guidelines for Life Sciences and Medical Research Involving Human Subjects (Notice No. 1 of the Ministry of Education, Culture, Sports, Science and Technology, the Ministry of Health, Labour and Welfare, and the Ministry of Economy, Trade and Industry, dated March 23, 2021)." All members of the research team who contributed to the development and implementation of this study by supporting data collection, analysis, interpretation, or publication of the study will be credited as authors. Each author is given sufficient time to

review the manuscript and the opportunity to approve it. This study is pre-registered at <https://www.umin.ac.jp/> (UMIN000048732).

## **8.2. Ethics Approval and Informed Consent**

This trial protocol is approved by the Ethics Committee for Medical Research at the University of Fukui (Approval Number: 20220054). Written informed consent is obtained from all participants, and the study is conducted in accordance with the Declaration of Helsinki and good clinical practice guidelines.

## **8.3. Individual Benefits, Burdens, and Risks Associated with Study Participation**

Participants will have free access to the Internet Cognitive Behavioral Therapy (ICBT) program for 12 weeks.

Participants will be responsible for the cost of TAU, but the guided ICBT will be free of charge. Participants will receive a compensation of 12,000 yen after completing the intervention or waitlist, regardless of group assignment. This includes the length of time the patient spent on the study and the difficulty of patient recruitment. To participate in this study, a referral letter from some hospitals is required, and participants may be responsible for the cost. Data collection and payment of compensation will be conducted by the research staff of Fukui University.

The content of the diagnostic interview and modules may cause negative emotions or feelings of fatigue in participants. For this reason, participants are informed that they have the right to pause or end the study at

any time, and that they will not be disadvantaged in any way. In addition, exclusion criteria are set to ensure that individuals in an acute stress state do not participate in ICBT, and strict checks are carried out before the study begins. Furthermore, in preparation for psychological stress, all participants are provided with the contact details of the research staff at Fukui University, and a system is in place to ensure that they can receive support if necessary. During the research period, all participants (waiting list group and intervention group) can continue to receive outpatient psychotherapy, medical treatment, and other treatment that they have been receiving up to this point. This research will be conducted online, but since the participants are those who are already regularly visiting medical institutions, including those who live far away, there is a system in place that allows them to promptly visit a nearby doctor if necessary.

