## 2. Introduction

Bulimia nervosa (BN) is an eating disorder characterized by recurrent episodes of binge eating followed by compensatory behaviors, such as purging or excessive exercise, and a persistent preoccupation with body shape and weight. Individuals with BN often experience body image distortion, perceiving their bodies as larger or heavier than they actually are, despite maintaining a normal or even underweight body weight. This distorted body image drives the compulsive engagement in purging, fasting, or excessive exercise to alleviate perceived physical flaws. Body image distortion encompasses both perceptual disturbances, such as misperceptions of body size and shape, and cognitive distortions, such as negative body image and dissatisfaction. Repeated cycles of binge eating and compensatory behaviors can lead to significant physical and psychological health consequences. Purging behaviors, particularly self-induced vomiting, can result in a range of physical complications, including dental erosion, electrolyte imbalances, esophageal tears, and salivary gland enlargement. From a psychological perspective, individuals with BN often experience a host of mental health issues, such as low self-esteem, self-harm, suicidal ideation, depression, anxiety disorders, sleep disturbances, and chronic fatigue.

Epidemiological studies have consistently demonstrated a high prevalence of eating disorders, particularly among women. In Western countries, approximately 2.6% of women are affected. Moreover, the overall prevalence of eating disorders has shown a significant increase, rising from 3.5% between 2000 and 2006 to 7.8% between 2013 and 2018. A recent meta-analysis estimated a lifetime prevalence of eating disorders of 0.91% and a 12-month prevalence of 0.4%, with a lifetime prevalence of BN specifically at

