## **5. Method**

### **5.1. Intervention Group**

Participants allocated to the intervention group are recommended to engage in a 12-week therapist-guided ICBT program. This ICBT program, consisting of 12 sessions, is based on a treatment model focused on psychoeducation about BN and modification of characteristic cognitive-behavioral patterns. Participants in this group receive weekly reminder emails to complete the ICBT program. The ICBT program includes videos, text, illustrations, and diagrams to facilitate self-guided CBT practice. The participants are able to access the ICBT program through their own devices. It is expected that each session can be completed within 15 minutes. Table 1 provides a description of the treatment modules and CBT techniques implemented in the ICBT program. At the end of each session, participants are assigned homework, requiring them to practice the learned CBT

skills tailored to their specific BN characteristics and report back to their therapist. Participants in the intervention group can consult with their therapist at any time via the chat system regarding any aspect of BN treatment or the ICBT program. The therapist (SH, the first author) is an experienced expert in CBT for BN and one of the developers of the face-to-face CBT manual that serves as the foundation for this ICBT program. A secure web-based platform is used for communication between therapists and participants, distribution of program materials, and collection of assessments.

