## **5.2. Control Group**

Participants assigned to the control group are encouraged to continue their usual care (UC) at a Japanese psychiatric clinic on a regular basis. UC group participants are also informed that they will have the opportunity to receive the guided ICBT program in the future by being placed on a waiting list. Control group participants are able to continue with counseling, antipsychotics, or other pharmacotherapy as needed, in consultation with their primary care physician, based on their individual condition and needs. However, as a general rule, it is prohibited to start or change any secondary therapies such as medication or counseling during the study period. Participants are asked to immediately report to the study office if there are any additions or discontinuations of medication therapy in unavoidable circumstances. It is planned that all changes will be documented in writing, along with the reasons.

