#### **Exclusion criteria:**

- (1) Serious mental disorders such as organic brain disorders, psychotic disorders, and drug dependence.
- (2) Imminent risk of suicide.

(3) Repeated engagement in antisocial behavior.

(4) Serious progressive physical disease.

(5) Difficulty in exposure to feared objects due to severe stress reactions or dissociation symptoms due to acute stress disorder or posttraumatic stress disorder.

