### **6.3. Exploratory Analyses and Additional Statistical Tests**

To assess treatment satisfaction and therapeutic alliance, the post-treatment mean values will be calculated for the intervention group. To evaluate baseline differences between the two groups, independent samples t-tests, chi-square tests, and Fisher's exact tests will be used. For the binary outcome of remission in bulimia nervosa (BN), a chi-square test will be employed to assess the significance of the odds ratio (OR). The criteria for remission will be determined using the cutoff values of the EDE-Q score, 2.34 or 2.80.

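### The protocol names distress from its modules as a risk but plans no adverse-event or deterioration collection, so a conclusion of benefit and acceptance would carry no balanced statement on individual worsening

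*Protocol*

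**What the plan says.** **Risk and response.** Section 8.3 states that "The content of the diagnostic interview and modules may cause negative emotions or feelings of fatigue in participants". The responses it lists are the right to pause or stop, the exclusion criteria (of which it says "strict checks are carried out before the study begins"), a support contact ("all participants are provided with the contact details of the research staff at Fukui University") and access to a local doctor. None of these is a record of what happened to participants.

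**Suicidality.** The Introduction says that "individuals with BN often experience a host of mental health issues, such as low self-esteem, self-harm, suicidal ideation, depression". Section 5.4 then lists "Imminent risk of suicide" as an exclusion. No dedicated measure of it is named after eligibility.

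**Measures.** Sections 5.6.3 to 5.6.7 give the weekly binge and compensatory counts (telephone, independent assessors), EDE-Q, PHQ-9, GAD-7, EQ-5D-5L, BBQ, CSQ-8 and WAI-SF. The only assessment times stated in 5.6 are baseline and 12 weeks, for the primary outcome.

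**Channels by arm.** Under 5.1, "Participants in the intervention group can consult with their therapist at any time via the chat system", and homework is reported back to the therapist. Under 5.2 (Control Group), "Participants are asked to immediately report to the study office if there are any additions or discontinuations of medication therapy in unavoidable circumstances", with changes and reasons put in writing. Section 5.1 has no matching sentence.

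**Analysis.** Section 6.2 compares groups and change over time. Section 6.3 dichotomises only remission. For the acceptance hypothesis in 4.1.2, the plan is: "To assess treatment satisfaction and therapeutic alliance, the post-treatment mean values will be calculated for the intervention group".

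**The concern.** The programme asks participants, who may be as young as 13, to carry out behavioural experiments, graded and cue exposure, and rescripting of painful memories (Table 1). Some of them may be upset by it or get worse even if the average participant improves. As planned, the trial could report a mean benefit and a good satisfaction score without counting those people or asking about them.

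Three features combine:

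- There is no prompted harm question in either arm.
- The scales that could show worsening are summarised as group differences, and the one clinical category is an improvement category.
- What participants volunteer depends on the route open to them, and the routes differ by arm. In the ICBT arm one route is the treating therapist, who helped develop the face-to-face manual on which the programme is based.

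The acceptance result has a related weakness. It is a post-treatment mean in the ICBT arm, so it describes those who answered.

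**Working it through.** **1. What each source can show about harm**

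| Source | Arms | Prompted? | Planned use |
|---|---|---|---|
| Weekly binge and compensatory counts (5.6.3, 5.6.4) | both | yes, blinded telephone | group difference (6.1, 6.2) |
| EDE-Q, PHQ-9, GAD-7 (5.6.5, 5.6.6) | both | yes | group difference (6.2); EDE-Q also for remission (6.3) |
| Research staff contact (8.3) | both | no | none stated |
| Therapist chat and homework (5.1) | ICBT only | homework yes, harm no | none stated |
| Therapy-change reports (5.2) | written under control | on occurrence | documented with reasons; no analysis stated |
| CSQ-8, WAI-SF (5.6.7) | summarised for ICBT only | yes | post-treatment mean (6.3) |

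No row is a prompted question on adverse effects, self-harm or unplanned care, and no row yields a count of participants who worsened.

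**2. The plan's own figures (6.6)**

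Inputs: d = 0.9, two-sided alpha 0.05, power 80%, dropout 30%. The noncentral t distribution gives power 0.792 at 20 per group and 0.812 at 21, so the minimum is 21. Dropout: 21 / (1 − 0.30) = 30. Both stated figures reproduce. They bound the numbers available for harms: 30 per arm if all are reached, about 21 if dropout is as assumed.

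**3. What equal questioning would detect**

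P(at least one case in an arm) = 1 − (1 − p)^n, with p assumed:

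| p | n = 21 | n = 30 |
|---|---|---|
| 5% | 1 − 0.95^21 = 0.66 | 1 − 0.95^30 = 0.79 |
| 10% | 1 − 0.90^21 = 0.89 | 1 − 0.90^30 = 0.96 |

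If no case is seen, the one-sided 95% upper bound on the rate is 1 − 0.05^(1/n): 13.3% at n = 21 and 9.5% at n = 30.

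**4. What it would not do**

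Take assumed rates of 5% and 20% (not from the protocol). Two-sided 5% normal-approximation power is Φ[(0.15 − 1.96·s0)/s1], with s0 = √(2 × 0.125 × 0.875 / n) and s1 = √((0.05 × 0.95 + 0.20 × 0.80) / n).

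- n = 30: s0 = 0.0854, s1 = 0.0832, power about 42%.
- n = 21: s0 = 0.1021, s1 = 0.0994, power about 31%.

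A formal comparison of harms would be weak even with identical collection in both arms.

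**The case against.** A reader might infer more than the protocol supports:

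- **That nothing relevant is measured after screening.** This is not so. Episode counts, EDE-Q, PHQ-9 and GAD-7 are taken in both arms and compared between them. They would show an average worsening in bulimic symptoms, depression or anxiety.
- **That every channel differs by arm.** The blinded telephone assessment and the staff contact serve all participants, both arms continue usual care, and 5.2 gives controls a written reporting route of their own. Only the therapist chat and homework belong to ICBT alone.
- **That worsening and suicidality are risks the protocol named and then ignored.** Section 8.3 names negative emotions, fatigue and psychological stress. Suicidality appears as disease background and as an exclusion.
- **That an alarming questionnaire would lie unread until analysis.** The protocol does not say when forms are read, and it does not describe the individual PHQ-9 items. This cannot be concluded from silence.

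Two further objections have force. Counts of worsening and adherence tables could sit in an analysis plan that is not shown, and the small sample limits any comparison of harms. Neither removes the point. An analysis plan can re-summarise the PHQ-9 and the weekly count, but it cannot supply answers to questions that were never asked. The sample limit argues for description rather than testing.

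The figure of about 21 of 30 is the sample-size dropout allowance, not a forecast of CSQ-8 and WAI-SF response. That participants who left in distress would be the least likely to answer is plausible but not documented.

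**Conclusion.** The point stands in this form: the protocol plans no adverse-event or deterioration collection although it names distress from its own modules. Systematic between-arm information on harm is limited to symptom scales analysed as group differences, and spontaneous reports come through unequal channels. The scales can show that an arm worsened on average. As planned, they do not show how many individuals did. With 12 weeks the only stated follow-up time, they can also miss transient distress and events in those who leave.

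In size, equal questioning of 21 to 30 per arm would probably reveal a harm affecting 10% (89% to 96%) and often one affecting 5% (66% to 79%). It would not support a powered comparison. These figures rest on assumed harm rates, complete answers from those contacted and truthful reporting. The conclusion itself rests on the text alone. It leaves the primary efficacy analysis and the sample size unaffected. It limits what may be said about harm and acceptance, and it should be corrected.

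**What to change.** 1. **Ask both arms the same questions.** At the week-12 telephone assessment, add a short fixed set on worsening, self-harm, unplanned care and upsetting effects of taking part, worded so that no arm is implied. Ask them after the primary count and after the assessor's treatment guess (6.5), so that neither the outcome nor the blinding indices are affected. Section 9 dates data collection as complete on 30 November 2024. If the call has passed, use a follow-up contact, since section 3 runs follow-up to October 2026. Because controls have delayed access to ICBT, such questions must refer to the randomised 12 weeks, and recall error must be acknowledged.
2. **Count worsening in 6.3.** Report by arm, descriptively, the number whose weekly combined count rose from baseline and the number who moved up a PHQ-9 severity band (bands in 5.6.6), with the number missing beside each. Some rises will be ordinary fluctuation, and the control arm shows how many to expect.
3. **Widen the acceptance result.** For all randomised to ICBT, report sessions completed and, where recorded, reasons for stopping, next to CSQ-8 and WAI-SF with their response counts.
4. **If step 1 is no longer possible,** state that harms were not systematically collected and limit the conclusions accordingly.

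The protocol should also say who reviews incoming questionnaires and when. Any clinical response is for the sponsor to set.

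The cost is a few minutes per call, two short tables and a small risk that an answer reveals allocation to the assessor. Steps 2 and 3 use planned outcome data and whatever session and withdrawal records exist.
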